### Study population and recruitment

The study population is recruited from diverse private and public organizations in the capital region and Pirkanmaa region in Finland. The participants are full-time employees with knowledge-intensive jobs. The contacted organizations have previously been interested in Tampere University recovery studies or belong to the network of the trainers delivering the intervention. We will first contact the organizations’ HR representatives by sending them an informational recruitment letter, followed by follow-up calls. Individual informational meetings with interested companies will be arranged.

After the company has agreed to participate in the study, we will forward our recruitment email to their employees. This email includes additional information about the study, including the timeline of the intervention. An organization can take part in the study if there are at least 12 employees interested in participating in the study. In each participating organization, a person will be appointed to facilitate the communication between participants, trainers, and researchers. This person will also provide the employees with a registration form (requesting employee’s name and contact information). Within each organization, we aim to assign participants randomly either to the intervention or to the waitlist control group. After the intervention, employers will receive an anonymized group feedback regarding the development of participants’ levels of stress, mental fatigue, job performance and organizational citizenship behavior across different measurement points.

### Training sessions

The training sessions take place on site for a maximum of 14 employees at a time. Trainers are experienced occupational well-being coaches trained by the researchers. Additionally, they have been actively involved in the intervention development process and are trained in various relaxation methods (e.g., yoga, meditation).

The first training session will focus on introducing the intervention, increasing awareness of stress, psychological needs and off-job crafting, reflecting on personal off-job crafting behaviors in small groups, and developing an individual off-job crafting plan for the intervention period. After a round of introductions, trainers will introduce theoretical findings about stress, off-job crafting and the DRAMMA model. Next, participants will work with their personal feedback reports and homework tasks to reflect on their psychological need satisfaction scores and off-job time activities first individually and then within small groups. The introduction section is followed by several practical exercises.

The practical psychological needs training is divided into six parts, each focusing on a specific DRAMMA need. First, trainers will provide a short theoretical overview of each dimension and a few examples of different strategies found to enhance that specific need. This is followed by a practical exercise addressing the same psychological need. For detachment from work, participants will be asked to think of a transition ritual [26] that would help them to clearly separate their work and non-work time. To introduce a relaxation strategy, the trainers will conduct a short relaxing stretching exercise. To enhance meaning, participants will engage in a short exercise that helps them to become aware of and act in accordance with their own personal values [27]. For mastery, they will engage in an exercise prompting them to remember a past success experience and to share it with another group member to increase participants’ self-efficacy [28]. After the mastery exercise, participants will engage in a strength spotting exercise to enhance affiliation [29]. Participants will take turns in sharing the strengths they have spotted in their colleague based on previously shared success stories to demonstrate how even brief positive interactions can increase the feeling of belonging and positive affect [30]. As participants share a personal story with each other, they get to know each other better and social bonds are strengthened. Finally, to increase autonomy, participants will learn about SMART goal setting [31]. Participants can find all the above described exercises and other training materials in the booklet which they will receive at the beginning of the first training session.

After the psychological needs training, participants will be asked to choose one psychological need that they wish to focus on during the four-week intervention period. While they are free to choose whichever of the six needs they want to work with, we recommend aiming to work with the psychological need that they scored the lowest on. This recommendation is made to support more balanced needs satisfaction across different needs, which has been found to be associated with higher reported well-being [32]. Participants will work in small groups and will be assisted by trainers to come up with their individual SMART off-job crafting goals. In the end, they will write their goals down in their personal booklets. As forming implementation intentions has been shown to improve goal achievement [33], participants will write a postcard for themselves where they outline how implementing their chosen DRAMMA goal will benefit them, what might potentially interfere with achieving the goal and how to overcome these barriers. The postcards will be sent to the participants during the second week of the four-week intervention as a positive reminder to continue working on their goals.

Next, participants will follow an app tutorial outlining the main functions of the smartphone app Everydaily and create their personal off-job crafting projects in the app. At the end of the first training session, trainers will summarize the main points of the training and the next steps, and participants will have a chance to ask questions about both this training session and the intervention in general.

After the four-week intervention period, participants will attend a second half-day training session. During this session, they first fill out the last weekly questionnaire and will receive new individual needs satisfaction scores, which they can compare to their baseline scores. Next, they have a chance to reflect on their experiences by identifying enablers and barriers that affected their off-job crafting during the intervention period. They will then review their previous goals, set future goals, and have the chance to ask questions. Additionally, we will ask participants to fill out a process evaluation questionnaire at the end of the training session to gather information about intervention reach, dose received and participants’ attitudes toward the intervention [34].

Both training sessions will include several short 10-min breaks between different parts of the training. During these breaks, participants can participate in additional exercises. On the first training day, participants can watch a video of natural surroundings to learn about the restorative effects of nature [35] and do a mindfulness meditation exercise. During the second training session, participants are offered to participate in progressive muscle relaxation exercise [36] and in a mandala coloring session with relaxing music [37].

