### Statistical analyses

#### Sample size calculation

The G*POWER software [64] was used to determine the minimum number of participants necessary to guarantee sufficient power of the study. Assuming an effect size of .25 (medium), alpha = .05 and power = .80, the required sample size is 64 participants per group to determine a significant difference between the intervention and the waitlist control group. Taking into account potential non-response and loss to follow-up, we aim to recruit at least 200 employees to ensure an adequate sample size.

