#### Basic analyses

All basic analyses are carried out with SPSS 25 [65]. Two-tailed significance level of < .05 will be considered statistically significant. Baseline characteristics of the participants are analyzed using descriptive statistics. Independent samples t-tests or chi-square tests are applied to check whether randomization was successful or whether there were systematic differences between the two groups. Preliminary analysis will be performed, including calculating descriptive statistics (i.e., means, standards deviations), factor analyses for all the scales, internal reliability calculations (Cronbach’s *α*) and bivariate correlations (Pearson’s *r*) between the study variables.

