#### Effect evaluation

We will use multilevel modelling techniques to test the change in outcome variables within subjects across seven measurement points before, during and after the intervention (i.e., within subject effect of participating in off-job crafting intervention). We will use Bliese and Ployhart’s [66] approach to estimate multilevel models in R, using the NLME library written by Pinheiro and Bates [67]. Additionally, we will test how participation in off-job intervention compared to control group affects the change in outcome variables across time (i.e., between subjects’ effect of the intervention compared to control group).

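### The 64 per group and the effect model described make no allowance for training-group clustering in the intervention arm, so 80% power is overstated and the between-group test is too liberal

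*Protocol article*

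**What the plan says.** Allocation is individual and within organisation (Study population and recruitment): "Within each organization, we aim to assign participants randomly either to the intervention or to the waitlist control group". An organisation may join with at least 12 interested employees.

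Delivery is in groups, in the intervention arm only (Training sessions): "The training sessions take place on site for a maximum of 14 employees at a time". Participants reflect in small groups, exchange success stories and spotted strengths with colleagues, and set goals in small groups with a trainer's help. The last weekly questionnaire is filled in at the second group session. Controls are offered the trainings only after the intervention.

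The sample size section states: "Assuming an effect size of .25 (medium), alpha = .05 and power = .80, the required sample size is 64 participants per group". The target is then raised to at least 200, for non-response and loss to follow-up only. No ICC or design effect appears.

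The effect evaluation uses multilevel models to "test the change in outcome variables within subjects across seven measurement points before, during and after the intervention", and adds a comparison of change between the arms. No training-group or organisation term is named. The limitations discuss contamination between colleagues but not clustering.

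**The concern.** People trained together share a trainer, a session and each other. Some exercises aim to strengthen bonds between them, and relatedness and affiliation are among the measured constructs. Their outcomes after training may therefore be correlated, while those of controls have no such source of correlation. This adds a between-group component to the variance of the intervention mean that neither larger groups nor more occasions per person remove.

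A model whose only random effects are for persons omits that component. Its standard error for the intervention effect is then too small, and false-positive claims become more frequent than 5%. A sample size derived for independent people also promises more power than a valid test has.

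**Working it through.** **Reproducing the plan's figure.** Inputs from the sample size section: effect size .25, alpha .05, power .80. The basic analyses section makes tests two-tailed.
- Two-sample t-test with d = 0.5: 63.8, so 64 per group; power at 64 is .801.
- One-way ANOVA with f = .25 and two groups: 127.5 in total.
- Read as d = .25, about 252 to 253 per group would be needed. So .25 is Cohen's f, equal to d = 0.5.

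The 64 is therefore a single comparison of independent people. With 200 recruits, the implied tolerable loss is 1 − 128/200 = 36%.

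**Allowing for training groups.** Let m be the number analysed per training group and ρ the training-group ICC. Clustering is in one arm only, and the total variance is set to 1 in both arms.
- Design effect in the intervention arm: DE = 1 + (m − 1)ρ
- Variance of the contrast with n per arm: (1 + DE)/n, against 2/n under independence; the inflation is (1 + DE)/2
- Type I error of the test that ignores groups: 2[1 − Φ(1.96/√inflation)]
- Power of a valid test: Φ(0.5/√((1 + DE)/n) − 1.96)
- n per arm for 80% power: (1 + DE) × ((1.96 + 0.84)/0.5)² = (1 + DE) × 31.4
- Tolerable loss from 100 recruited per arm (equal split assumed): 1 − n/100

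**Group size.** Fourteen is the stated maximum. Twelve employees split equally give 6 per arm. One hundred people in sessions of at most 14 need at least 8 groups (100/14 = 7.1), so 64 completers spread over 8 groups are 8 per group.

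**Worked case, m = 14, ρ = .05, n = 64.** DE = 1 + 13 × .05 = 1.65 and inflation = 2.65/2 = 1.325. Type I error = 2[1 − Φ(1.96/1.151)] = 8.9%. The standard error is √(2.65/64) = .2035, so power = Φ(2.457 − 1.96) = 69%. For 80% power, 2.65 × 31.4 = 83.2, so 84 per arm; tolerable loss is 16%.

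| Analysed per group | ICC | DE | Type I error, 64 per arm | Power, 64 per arm | n per arm for 80% | Tolerable loss | Power, 100 per arm |
|---|---|---|---|---|---|---|---|
| 6 | .02 | 1.10 | 5.6% | 79% | 66 | 34% | 93% |
| 6 | .05 | 1.25 | 6.5% | 76% | 71 | 29% | 92% |
| 6 | .10 | 1.50 | 8.0% | 72% | 79 | 21% | 89% |
| 8 | .02 | 1.14 | 5.8% | 78% | 68 | 32% | 93% |
| 8 | .05 | 1.35 | 7.1% | 74% | 74 | 26% | 90% |
| 8 | .10 | 1.70 | 9.2% | 68% | 85 | 15% | 86% |
| 14 | .02 | 1.26 | 6.5% | 76% | 71 | 29% | 91% |
| 14 | .05 | 1.65 | 8.9% | 69% | 84 | 16% | 87% |
| 14 | .10 | 2.30 | 12.7% | 60% | 104 | none | 79% |

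These are normal approximations (which give 81% at 64 per arm without clustering). With few training groups, small-sample degrees of freedom would lower power somewhat further.

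**Organisation.** Trials randomised within organisation were simulated with an organisation intercept (ICC .05 and .10) and no training-group effect, and analysed by an unadjusted t-test (20,000 runs per setting; 5 organisations of 13 per arm, or 8 of 8). Type I error was 4.2 to 4.8% and power 81 to 83%, so omitting organisation is slightly conservative.

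**The case against.** Several points on the other side stand.

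- **The ICC is in no document.** At .01 to .02 with groups of 6, power at 64 per arm is still 79 to 80% and type I error 5.3 to 5.6%. The problem is material only if clustering is.
- **Fourteen is a ceiling, and 64 is what remains after loss.** Full groups of 14 with 64 analysed require loss to occur before groups form and every session then to be full. Six to 8 per group is as plausible.
- **Two hundred recruits leave room.** If all 100 per arm are analysed, power is at least about 79% throughout the table. The protocol, however, gives that margin to attrition alone, and extra people do not correct the type I error of a test that ignores groups.
- **The planned analysis uses baseline and repeated measures.** This may recover some power compared with the single comparison behind the 64. It does not remove between-group variance in the effect, so the type I error remains.
- **The article names multilevel modelling without listing every random effect.** A separate analysis plan could add a training-group term, and the article does not exclude one. Such a plan would not change the power figure stated here, which rests on independence.

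A reader might also infer that leaving organisation out of the model makes the test too liberal. The documents do not support that: allocation is within organisation, so its main effect is balanced between arms and omitting it costs only precision.

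**Conclusion.** The point holds for training groups. The protocol describes group delivery in one arm, states a sample size that assumes independent people, and names no nesting above the person. For any positive training-group ICC, an analysis as described is too liberal and a valid test at 64 per group has less power than on the protocol's own single-comparison basis.

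The size depends on an assumed ICC and group size. Over ICC .02 to .10, type I error is about 6 to 9% and power 79 to 68% with 6 to 8 analysed per group; full groups of 14 are the worst case. A reader might infer that the trial is underpowered as recruited. The figures do not show that: 200 recruits can still give about 80% power or more in most settings if losses are modest. What shrinks is the loss that can be tolerated.

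**What to change.** **Effect evaluation.** Add a random effect for training group in the intervention arm only, acting on the intervention effect over time (the baseline questionnaire precedes the training), with small-sample degrees of freedom. Include organisation as a stratification factor; it is the randomisation stratum, so this is a precision gain at no cost.

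**Sample size calculation.** State that .25 is Cohen's f (d = 0.5). Restate power, and the loss that 200 recruits can absorb, over a stated range of ICCs and realistic group sizes.

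**Cost.** A less favourable power statement and slightly wider intervals. Session and organisation membership should be known from running the trainings, so no new data collection and no extra participants are required. If the ICC were as high as .10 with full groups of 14, 104 per arm would be needed and 200 would not quite reach 80% power on this basis; the restated figure should say so.

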**Fig. 1 Fig1:**
[figure not shown]
Off-job crafting intervention design

The study will be carried out in Finland from October 2019 to May 2020. All participants who have given informed consent to participate in the study will first fill out an online baseline questionnaire, concerning demographics (e.g., age, gender, education), basic job information (e.g., work hours), off-job and job crafting, psychological needs, well-being (e.g., mental fatigue, work engagement) and performance (e.g., family role performance, organizational citizenship behavior) 2 weeks before the intervention period. Additionally, intervention group participants will receive a small task to complete before the first training session. The task consists of composing a list of things that the participant likes and dislikes doing during their off-job time. In addition, they are asked to take two picture that represent: 1) an activity that they loved doing over the past week and 2) an activity that they did not like to do during their off-job time. One week before the first training session, participants will receive a reminder to complete the questionnaire and the homework task. Two weeks after the baseline measurement, intervention group participants will take part in a half-day long training session. Shortly before the training, each intervention group participant receives a personal feedback report containing information about their baseline scores on DRAMMA needs satisfaction and comparison of their scores to reference values derived from other published scientific studies with Finnish and European knowledge workers as the reference group [23–25]. During the four-week intervention period, every Tuesday, intervention group participants will receive an email with a link to a weekly online questionnaire. In case of non-response, reminders will be sent on Wednesdays and Thursdays. The control group will be asked to fill out a second questionnaire immediately after the end of the intervention period of the intervention group. Additionally, participants from both groups will receive the same online questionnaire via email twice during the post-intervention period (two and six weeks after intervention). After the intervention period, the intervention group will participate in a half-day long reflection session.

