#### Process evaluation

At the end of the second training session, a process evaluation will be conducted to provide insights into the process of the intervention and the mechanisms that might have influenced the effectiveness of the intervention. Participants are asked to indicate the extent that they participated in the intervention, the level of effort invested in following the intervention, and whether they perceived participation in the intervention to be time-consuming. Additionally, we ask them to report their level on enjoyment and satisfaction with the intervention, relevance of the training content, and the type of perceived support that they received from others during the intervention. We also ask participants to assess whether they gained new skills and knowledge from the intervention, and to express their level of satisfaction with the performance of the trainers during on-site trainings. Regarding the smartphone app Everydaily, we ask participants to indicate how many Dailys they have completed and whether they also logged all the completed Dailys to the app to gain better understanding about participants’ app use. Regarding off-job crafting goal setting, participants are asked to indicate the psychological need that they worked on during the intervention period and write down the goal that they set during the first training session. They are then asked to rate their goal attainment during the intervention period on a scale from 0 to 100%. Finally, participants can describe the most important things that they learned during the intervention and provide any additional comments.

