### Strengths and limitations

The main limitation of the study is that the intervention includes several on- and offline components. With the two-armed randomized control trial (intervention versus waitlist control), it is not possible to evaluate each specific component separately, and it is therefore difficult to establish which intervention components are the most effective. However, we aim to conduct a thorough process evaluation to gain insights into recruitment, reach, fidelity, participants’ attitudes toward the intervention, context, implementation, dose delivered and dose received, and to link the effect and process evaluation results to better understand the different mechanisms that might have influenced the effectiveness of the intervention [34]. Secondly, as the intervention and the waitlist control group participants are recruited from the same organization and potentially form the same departments, contamination may occur. While the trainings, booklets and smartphone app are first only made available for the intervention group, there is still a chance that colleagues participating in the intervention could share their training materials with the waitlist control group participants. To minimize this risk, intervention participants are specifically reminded not to share the training materials with the control group members until the end of the intervention period. Thirdly, another limitation might be participants’ non-adherence to the instructions or dropping out of the study entirely. In order to avoid these potential complications, we will explain the procedures to the participants carefully both in the informed consent form and during the first training session to remind participants about the importance of following the entire intervention program. We will also send them a mid-intervention postcard reminder and will monitor closely the weekly questionnaire response rates, sending reminders to those who do not fill out the questionnaires by the deadlines indicated in the emails. We will further assess adherence to the intervention program with the process evaluation.

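### The intervention arm completes the end-of-intervention questionnaire on site at the second training session while controls have no session, and the process evaluation is collected only from those who attend it

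*Protocol article*

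**What the plan says.** Under Study design, the intervention arm's weekly questionnaires go out electronically: "every Tuesday, intervention group participants will receive an email with a link to a weekly online questionnaire". Non-responders are followed up: "In case of non-response, reminders will be sent on Wednesdays and Thursdays". Strengths and limitations repeats that the team "will monitor closely the weekly questionnaire response rates, sending reminders to those who do not fill out the questionnaires by the deadlines".

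Under Training sessions, the last of these questionnaires is placed in the second half-day session, held after the four-week period: "During this session, they first fill out the last weekly questionnaire and will receive new individual needs satisfaction scores". According to the same section, sessions hold at most 14 employees and are led by trainers who helped to develop the intervention.

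Controls have no session at this point. Study design says: "The control group will be asked to fill out a second questionnaire immediately after the end of the intervention period of the intervention group". For the two later waves it says that "participants from both groups will receive the same online questionnaire via email twice during the post-intervention period".

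The process evaluation has one stated collection point: "At the end of the second training session, a process evaluation will be conducted". Training sessions says that it gathers information on reach and dose received. Strengths and limitations adds: "We will further assess adherence to the intervention program with the process evaluation". That section also plans to link the process results to the effect results.

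**The concern.** All the outcomes are self-reports, and they include job performance and organizational citizenship behavior. At this wave one arm rates them in a training room with colleagues and trainers present. The other arm does not. A difference in setting that coincides with treatment arm cannot be separated from the treatment effect by any model.

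The wave also has a particular role. Controls receive no questionnaire in weeks 1 to 3, so this is the only between-arm comparison before the two-week follow-up. Under Measures, off-job activities are recorded only at baseline and in the fourth weekly questionnaire, so a missed fourth questionnaire loses the only post-baseline value of that variable.

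Selection is the second problem. Participants who skip the reflection session are plausibly the less engaged. A reach and adherence form handed out only at that session does not describe them, and any analysis linking adherence to effect would rest on attenders alone.

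**Working it through.** **1. Which waves compare the arms.** The intervention arm has 1 baseline + 4 weekly + 2 follow-up = 7 questionnaires. The control arm has 1 baseline + 1 at the end of the intervention period + 2 follow-up = 4. The arms therefore meet after baseline at three waves:

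| Wave | Intervention arm | Control arm |
|---|---|---|
| End of intervention | On site, start of second session | Second questionnaire, no session; place not stated |
| Two weeks after | E-mail | E-mail |
| Six weeks after | E-mail | E-mail |

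Only the first row differs by arm.

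**2. Route for absentees.** Study design gives the weekly questionnaires an e-mailed link and reminders. Training sessions puts the last one in the session. Neither section says that the fourth questionnaire leaves the e-mail route, and neither says that an absentee still gets the link. Both readings are open.

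**3. Process evaluation.** Training sessions and Process evaluation both place it at the end of the second session, and no other route is given. Let q be the share of the intervention arm absent from that session, a the adherence among attenders and b the adherence among absentees. Adherence over the whole arm is (1 − q)a + qb. The form estimates a, so it overstates by q(a − b), which is positive whenever absentees adhere less. Reach of the second session, read from the form alone, is 100%, because everyone who fills it in was there. Actual reach is 1 − q.

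**4. Scale of a possible effect on outcomes.** The plan's own figure comes first. Sample size calculation assumes effect size 0.25, alpha 0.05 and power 0.80, and gives 64 per group. Read as Cohen's f, 0.25 corresponds to d = 2 × 0.25 = 0.5. The normal approximation gives 63 per group and the exact t test gives 63.77, rounded up to 64. The figure is reproduced, and 0.5 SD is the planning effect.

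The article gives no non-attendance rate, so q is assumed to be 0.1 to 0.3. Suppose also that absentees would score s SD worse than attenders. An unadjusted attenders-only mean is then too favourable by q × s:

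| q | s = 0.25 | s = 0.5 |
|---|---|---|
| 0.1 | 0.025 SD | 0.05 SD |
| 0.2 | 0.05 SD | 0.10 SD |
| 0.3 | 0.075 SD | 0.15 SD |

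These figures apply only if absentees really do lack the fourth questionnaire and the analysis makes no use of their other waves.

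**5. Power.** Assume 100 per arm (the target of 200 split equally; the ratio is not stated), d = 0.5, and loss in the intervention arm only. Power falls from 94.0% with no loss to 92.8%, 91.2% and 89.1% at q = 0.1, 0.2 and 0.3. Loss of power is not the issue.

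**The case against.** The strongest reply is that the article never says absentees go unmeasured on outcomes. The e-mailed link and reminders are described twice and not withdrawn, and the abstract calls all assessments online. This stands. A reader might infer that non-attenders are lost to the outcome analysis at this wave, but the text shows only that their route is not settled.

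A reader might also infer a large upward bias at a key end point. If absentees gain nothing and attenders gain 0.5 SD, the effect over all randomised participants is 0.5(1 − q), and the attenders-only figure is inflated by 1/(1 − q): 1.11, 1.25 and 1.43 at q = 0.1, 0.2 and 0.3. The documents do not support that reading, for three reasons:

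- Zero benefit is an assumption. An absentee may already have had the first training, the crafting plan and the app.
- Effect evaluation plans multilevel models over seven measurement points. These can retain a participant's other waves and so account for some of the selection.
- No primary time point is named, and two further between-arm comparisons use the same e-mail route.

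On setting, the questionnaire comes first in the session, so neither the new scores nor the session content can have shaped the answers. Nothing says that trainers or colleagues see them. The direction of any setting effect is therefore not shown. The difference in setting remains.

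On adherence, weekly response rates are also monitored, and attendance at a small on-site session is easy to observe. The process evaluation is thus not the only possible source. However, the article does not say that attendance will be counted in the adherence figures or that app logs will be analysed, so the selection in the form itself remains.

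**Conclusion.** The point holds in a limited form. Three things follow from the text: the response setting differs by arm at the end-of-intervention wave; Study design and Training sessions are not reconciled on how the fourth questionnaire is delivered; and the process evaluation has no stated route to people who miss the second session.

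The reach and adherence figures will tend to be too high, by q(a − b) for adherence. This rests on the assumption that absentees adhere less. For the outcome effect, neither size nor direction is established. The 0.025 to 0.15 SD range illustrates what selection could do under assumed absence and an unadjusted comparison; it is not an estimate for this trial. The two- and six-week comparisons are not touched. The change is worth making because it is cheap and removes an avoidable difference between arms.

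**What to change.** 1. Send the fourth questionnaire to both arms through the same online link at the same time, to be completed before the second session, with the same reminders and including those who will not attend. Score feedback can still be given at the session.
2. Send the process evaluation online to intervention participants who do not attend.
3. Record session attendance, and count non-attendance in the adherence and reach figures.
4. Make Study design and Training sessions agree on the delivery route.

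The cost is one re-timed link and one extra e-mail. The downside is possibly slightly lower completion than on site. To limit it, attenders who have not yet responded can complete the link at the session, with the place of completion recorded so that its influence can be examined.
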